### 2.3. Eligibility Criteria

Trained psychiatrists/psychologists will review the diagnosis of depression using the Brazilian version of the Mini International Neuropsychiatric Interview 5.0.0 (MINI) [19], which was developed based on the *Diagnostic and Statistical Manual of Mental Disorders*, 4th edition (DSM-IV) and International Classification of Diseases and Related Health Problems, 10th revision (ICD-10). 

Inclusion criteria are: (a) age between 18 and 60 years; (b) diagnosis of major depressive disorder or depressive episode in bipolar disorder according to DSM-IV; (c) baseline HAMD17 score ≥17; (d) current TDR episode; (e) appropriate clinical condition for receiving ECT as assessed by a psychiatrist and an anesthesiologist; and (f) meeting transcranial magnetic stimulation (TMS) safety criteria [20]. In the definition of TRD for major depressive disorder, the utilization of a minimum of two prior treatment failures will be considered. Conversely, for TRD in bipolar depression, only one prior treatment failure will be required. In both cases, there must be confirmation of prior adequate dose and duration, based on clinical criteria evaluated using the Antidepressant Treatment History Form (ATHF) [21,22].

Exclusion criteria are: (a) pregnancy; (b) psychiatric comorbidity (except mild anxiety disorders); (c) depressive symptoms better explained by other clinical conditions or psychiatric disorders; (d) decompensated clinical and neurological conditions or serious sequelae of previous medical conditions; (e) use of psychoactive substances in the last 6 months (except nicotine); (f) use of monoamine oxidase inhibitors in the last 6 months; (g) application of ECT or another neuromodulation technique in the last 12 months; (h) contraindications for ECT or MRI; (i) relevant deviations in clinical laboratory parameters; or (j) inability to consent.

Discontinuation criteria are: (a) worsening depression; (b) development of suicidal ideation or suicide attempt; (c) withdraw consent; (d) development of (hypo)manic symptoms; (e) inability to induce seizures lasting at least 15 s after adjusting parameters and medications during the titration phase; (f) missing two consecutive treatment sessions; or (g) changes in drug treatment without the previous authorization.

Patients will need to have a stable drug regimen for at least 2 months before the first clinical and neuroimaging evaluations. Medications that alter the seizure threshold, such as benzodiazepines and mood stabilizers with anticonvulsant action, will be closely monitored. If necessary, the team will evaluate the possibility of reducing the doses of these medications before the second titration session.

These eligibility criteria are consistent with the criteria employed in important ECT trials conducted in recent years [23,24,25] and another comparative study protocol between ECT and MST [26].

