## Abstract

Treatment-resistant depression (TRD), characterized by the failure to achieve symptomatic remission despite multiple pharmacotherapeutic treatments, poses a significant challenge for clinicians. Electroconvulsive therapy (ECT) is an effective but limited option due to its cognitive side effects. In this context, magnetic seizure therapy (MST) has emerged as a promising alternative, offering comparable antidepressant efficacy with better cognitive outcomes. However, the clinical outcomes and cognitive effects of MST require further investigation. This double-blinded, randomized, non-inferiority study aims to compare the efficacy, tolerability, cognitive adverse effects, and neurophysiological biomarkers of MST with bilateral ECT (BT ECT) in patients with TRD. This study will employ multimodal nuclear magnetic resonance imaging (MRI) and serum neurotrophic markers to gain insight into the neurobiological basis of seizure therapy. Additionally, neurophysiological biomarkers will be evaluated as secondary outcomes to predict the antidepressant and cognitive effects of both techniques. The study design, recruitment methods, ethical considerations, eligibility criteria, interventions, and blinding procedures are described. The expected outcomes will advance the field by offering a potential alternative to ECT with improved cognitive outcomes and a better understanding of the underlying pathophysiology of depression and antidepressant therapies.

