## 1. Introduction

Depression is a prevalent global health issue, affecting more than 264 million people worldwide, according to the World Health Organization (WHO)**.** However, a significant proportion of individuals with depression do not achieve symptomatic remission even after multiple appropriate pharmacotherapeutic treatments. This condition is known as treatment-resistant depression (TRD) [1]. Managing TRD poses challenges for clinicians, as they must rule out misdiagnosis, comorbid disorders, inadequate therapeutic regimens, and non-compliance with treatment before considering additional strategies such as electroconvulsive therapy (ECT) [2].

Although ECT is an effective treatment for TRD, its cognitive side effects, such as impaired mnesic and non-mnesic abilities, limit its broader use [3]. While non-mnesic abilities impairment and anterograde amnesia generally improve within 15 days after the last ECT session, retrograde amnesia can persist for years, making it the most concerning cognitive side effect of ECT [4,5,6].

Recent years have witnessed the emergence of innovative treatments for mental disorders, including psychedelics and alternative agents. Some of these drugs, such as ketamine and dextromethorphan, target NMDA receptors and offer potential for more favorable clinical profiles. Nevertheless, further research is needed to understand their underlying mechanisms and develop effective treatments [7,8].

The lack of a clear understanding of the pathophysiology of depression and antidepressant therapies also hampers the development of neuromodulation techniques, including convulsive therapies. Although various strategies have been developed to mitigate ECT-induced cognitive effects, their results have been limited [9]. One possible explanation is that electrical stimulation diffuses throughout the brain, including deep structures crucial for memory retention, due to the high resistance offered by the skull and scalp [10].

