### 2.1. Study Design, Setting, and Recruitment

The study involves a double-blinded, randomized, non-inferiority clinical trial [14] with two treatment arms (see Figure 1: study design) conducted at the Institute of Psychiatry, Hospital das Clínicas, São Paulo, Brazil.

Recruitment will be conducted through referrals from physicians in the ECT Service (mainly from the Institute of Psychiatry), self-referral via university community advertisements (e.g., leaflets and email), and advertisements on the website (www.sin.org.br), Google, and social media platforms such as Facebook.

After the recruitment and selection process, participants will undergo a baseline assessment, which includes medical evaluation, neuropsychological assessment, laboratory tests, and cranial MRI. They will then be divided into two groups (ECT and MST). The study will utilize a 1:1 controlled randomization model with blocks of random sizes and lengths generated through www.sealedenvelope.com.

Generally, during the acute phase of ECT, the frequency of treatment sessions varies from one to three times per week. Studies have indicated that ECT conducted twice a week shows comparable efficacy to ECT performed three times a week, while requiring a reduced number of treatments. Additionally, there appears to be greater efficacy of ECT applied three times a week compared to the weekly application schedule [15]. Regarding cognitive functioning, the more frequent the sessions, the greater the cognitive impairments [16]. Consequently, we have opted to conduct ECT or MST sessions during the active phase with a frequency of twice a week on non-consecutive days.

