We will define adverse events as events with intensity greater than “mild” and at least “remotely” associated with the intervention, as carried out in our previous studies [31]. The presence of adverse events and (hypo)manic upset will be compared between groups E and C using the chi-square test. This test will also be used to assess whether allocation group guessing occurred beyond chance.

Regarding the BDNF data, each collection during the follow-up will be individually analyzed in relation to the baseline values using Student’s *t*-test. The same analysis will be conducted to assess the differences between the treatment groups (ECT x MST) at each endpoint. Additionally, analysis of variance (ANOVA) will be used to evaluate potential differences in the means of plasma BDNF at different collection time points. A significance level of 5% will be adopted for all tests.

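### Diagnosis (unipolar or bipolar) is collected at entry, but the text shown uses it neither as a stratum nor as a covariate: a small, avoidable loss of precision and interpretability, mainly for the (hypo)mania comparison

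*Protocol article*

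**What the plan says.** All references are to the Protocol article.

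- **Population (2.3).** Entry requires "diagnosis of major depressive disorder or depressive episode in bipolar disorder according to DSM-IV". For major depressive disorder, "the utilization of a minimum of two prior treatment failures will be considered". For bipolar depression, "Conversely, for TRD in bipolar depression, only one prior treatment failure will be required". Both are to be confirmed on the ATHF. Diagnosis is established with the MINI. No quota or expected bipolar share is given.
- **Randomisation (2.1).** A "1:1 controlled randomization model with blocks of random sizes and lengths generated through www.sealedenvelope.com". No stratification factor is named.
- **HAMD17 (2.9).** Non-inferiority rests on the difference between arm means with its 95% confidence interval after session 12. No covariate is named.
- **AMT (2.9).** The model adjusts for age, schooling and treatment-resistant depression. Diagnosis is not listed.
- **(Hypo)mania (2.9).** "The presence of adverse events and (hypo)manic upset will be compared between groups E and C using the chi-square test". No stratification is mentioned.

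**The concern.** Diagnosis is fixed before randomisation, recorded for every patient, and defines two groups admitted under different thresholds. It is a plausible predictor of treatment-emergent (hypo)mania and possibly of HAMD17, although the documents give no figure for either.

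With about 50 patients per arm and no stratum, the arms can end up with visibly different bipolar shares. Two things are then given up:

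- **Precision.** An analysis that ignores a prognostic baseline factor leaves its variance in the error term.
- **Interpretability.** If a few more (hypo)manic events occur in one arm and that arm also has more bipolar patients, the pooled chi-square cannot separate the mix from the device.

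The second matters more, because (hypo)mania is likely to be a sparse outcome.

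**Working it through.** **1. The plan's own sample size.** Inputs from 2.10: margin 5.7, SD 9.5, one-sided α 0.025, power 80%.

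n per arm = 2 × (1.960 + 0.842)² × 9.5² / 5.7² = 43.6, so 44 per arm and 88 in total. This matches the stated 88. Allowing for 10% attrition, 88 / 0.9 = 98, against the stated 100 (50 per arm).

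**2. Chance imbalance.** Assume 100 patients split exactly 50/50, with K bipolar patients (K is not in the documents). The number x in one arm is hypergeometric, and the difference in share is |2x − K| / 50. For even K this moves in steps of 4 points.

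| Assumed bipolar share | P(difference ≥ 12 points) | P(difference ≥ 20 points) |
|---|---|---|
| 20% | 21% | 2% |
| 30% | 28% | 5% |
| 40% | 31% | 7% |

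**3. Effect on HAMD17.** Assume polarity changes HAMD17 by 3 points.

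- Shift: 0.12 × 3 = 0.36 and 0.20 × 3 = 0.60 points.
- Standard error at 50 per arm: 9.5 × √(2/50) = 1.9.
- At the upper end, 0.60 / 1.9 = 0.32 standard errors and 0.60 / 5.7 = 11% of the margin.

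**4. What adjustment gains on HAMD17.** R² = share × (1 − share) × D² / 9.5², and adjusted SD = 9.5 × √(1 − R²).

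- At a 30% share and D = 3: R² = 0.21 × 9 / 90.25 = 2.1%, so the SD falls to 9.40. Power at 44 per arm (normal approximation) rises from 80.4% to about 81%.
- Over shares of 20-50% and D from 2 to 5.7, R² is 0.7-9.0%, power is 80.6-83.9% and the required N is 80-88.

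**5. Validity of the unadjusted HAMD17 test.** Simulated one-sided type I error at the margin, nominal 2.5%, is 2.5% (30% bipolar, D = 4) and 2.6% (50% bipolar, D = 5.7).

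**6. (Hypo)mania.** All rates are assumed. The simulation used 50 per arm and 60,000 replicates, with no continuity correction. Power is for a doubling of both rates in one arm.

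| Bipolar share | Rates, bipolar / unipolar | Type I error: chi-square | Type I error: Mantel-Haenszel | Power: chi-square | Power: Mantel-Haenszel |
|---|---|---|---|---|---|
| 30% | 15% / 1% | 4.5% | 4.5% | 15.1% | 17.2% |
| 30% | 30% / 2% | 5.1% | 4.7% | 31.5% | 38.8% |
| 50% | 15% / 1% | 4.6% | 4.7% | 24.3% | 25.0% |
| 50% | 30% / 2% | 5.6% | 5.1% | 47.2% | 57.9% |

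Both tests hold their level approximately. The stratified test gains about 1 to 11 points of power, and at least 2 points in three of the four scenarios.

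**7. Reading a single result.** Take 30 bipolar patients, rates of 15% and 1%, and no treatment effect.

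- An 18 v 12 split gives 18 × 0.15 + 32 × 0.01 = 3.0 expected events against 12 × 0.15 + 38 × 0.01 = 2.2.
- A 20 v 10 split gives 20 × 0.15 + 30 × 0.01 = 3.3 against 10 × 0.15 + 40 × 0.01 = 1.9.

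**The case against.** **The definition.** A reader might infer that bipolar patients fail the trial's own definition, since the Abstract describes TRD as "characterized by the failure to achieve symptomatic remission despite multiple pharmacotherapeutic treatments" and the Introduction speaks of patients who "do not achieve symptomatic remission even after multiple appropriate pharmacotherapeutic treatments". The documents do not support that. Those sentences are general background. Section 2.3 is the operational definition, and it states the threshold for each diagnosis openly. The Discussion also describes the population as unipolar or bipolar. At most the background wording could be aligned.

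**Bias.** A reader might also infer that a chance difference in mix invalidates the comparisons or determines their result. It does not. Randomisation makes the imbalance random, and the error rate of an unadjusted test already allows for it, as steps 5 and 6 show. On HAMD17 the shift is small beside the standard error and the margin. This objection stands in full, and it limits the point to precision and interpretability.

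**Discontinuations.** (Hypo)manic symptoms are a discontinuation criterion, so a reader might suspect that polarity distorts the modified ITT set, which requires at least 8 sessions. The documents give no rate from which to judge this.

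**Silence in a condensed article.** Stratification factors may be stated in the full protocol or SAP, so their absence from 2.1 is weak evidence by itself. That stands. However, 2.9 does fix a covariate list for AMT, a simple mean difference for HAMD17 and a pooled test for (hypo)mania, and diagnosis appears in none of them. The listed covariate of treatment-resistant depression does not clearly fill the gap. As a yes/no variable it would be constant, because every patient has TRD by inclusion criterion (d). As a degree of resistance it would only partly track diagnosis.

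**Conclusion.** The point holds as a minor, optional improvement. Nothing here invalidates a planned analysis.

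On HAMD17 the benefit is slight: about one point of power under an assumed 3-point polarity effect. On (hypo)mania a stratified test keeps its error rate, gains roughly 1 to 11 points of power in the scenarios tried, and makes a small difference in event counts easier to interpret. No size is computed for AMT, because the documents give nothing from which to judge a polarity effect on it.

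Every size rests on assumptions about the bipolar share, the event rates and the polarity effect. If diagnosis hardly predicts outcome, the gain is close to nil, and so is the cost.

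**What to change.** 1. Add diagnosis (unipolar/bipolar, from the MINI) as a baseline covariate in the HAMD17 comparison and the AMT model.
2. Replace the pooled chi-square for (hypo)manic upset with a Mantel-Haenszel test stratified by diagnosis.
3. If randomisation has not begun, the list may also be stratified by diagnosis. If the full protocol already does this, the first two changes simply bring the analysis into line.

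The cost is one covariate already in the database, one changed test and, if chosen, a two-level list. The sample size stays as it is. The changes should be written into the analysis plan before unblinding. A separate non-inferiority estimate in patients with two or more failures is not required; it would be imprecise.

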### 2.4. Interventions

#### 2.4.1. Anesthesia and Monitoring

We have developed anesthesia protocols based on the most recent evidence available in the literature [27] and the availability of resources in our setting. Basically, trained anesthesiologists with ECT experience will administer general anesthesia using etomidate (0.5 mg/Kg), succinylcholine (0.6 mg/Kg), and atropine (0.5–1 mg) to prevent cardiac arrhythmias. Patients will be ventilated with a 100% oxygen mask, and cardiovascular parameters will be monitored throughout the procedure. The seizure threshold (ST), which is the minimum energy required for a generalized tonic-clonic seizure, will be determined at the beginning of the study using specific protocols for each technique, which will be described below. Seizures will be considered adequate if they result in generalized tonic-clonic activity lasting more than 20 s of motor or electroencephalographic (EEG) activity, according to the guidelines of the American Psychiatric Association (1990) [28]. The EEG monitor of the Magventure (Farum, Denmark) MagPro MST device will be used for this purpose, which allows for digital storage of tracings for patients undergoing ECT and MST. 

#### 2.4.2. ECT

The ECT sessions will be conducted with the Thymatron System IV (Somatics LCC, Venice, FL, USA). The pulse width and amperage will be fixed at 0.5 ms and 0.9 A, respectively, while other parameters such as pulse frequency will be automatically determined by the device based on the selection of the operator. The electrodes will be positioned bilaterally in the temporal region, as this is associated with a more effective and rapid response to depressive symptoms [16]. The electrodes will receive conductive gel and will be positioned about four centimeters perpendicularly above the midpoint of an imaginary line between the lateral epicanthal fold and the tragus. These parameters are in accordance with the local practice of the ECT Service of the Institute of Psychiatry.

To determine the electrical load, a dose titration process will be conducted during the first session of each individual [29]. This process will begin with a 5% load (equivalent to 25 mC). If this stimulus is not effective in triggering an adequate generalized convulsive crisis, the load will be doubled and the stimulus repeated until an effective crisis is triggered or a maximum threshold of 3 to 4 attempts is reached, depending on the assessment of the psychiatrist and the anesthetist according to physiological parameters (blood pressure, oxygen saturation, heart rate) and depth of sedation. If a seizure is not initiated in the first session, a new titration session will be scheduled, and medication will be reviewed.

The second titration session will repeat the parameters used in the last attempt and will follow the same procedures described above. If seizures are still not initiated in the second session, the patient will be excluded from the study. In subsequent sessions after the titration, the load used will be two and a half times, rounding down when necessary. If the patient has seizures of less than 20 s duration, the load will be increased by 100% in the next session until the seizures are effective or the maximum load of the device is reached.

#### 2.4.3. MST

The MagVenture MagPro MST with Twincoil (Magventure, Farum, Denmark) will be used for MST sessions. The procedure will follow the same guidelines as ECT sessions regarding general anesthesia, oxygenation, motor activity monitoring, EEG, and postictal recovery. The Twin Coil will be centered over point Fz of the 10–20 system using an EEG cap to mark the correct point on the patient’s scalp.

The stimulation will be delivered with an amplitude of 100%, 100 Hz. In the first session, a titration of the convulsive threshold will be performed with a 2 s stimulus (200 pulses). If an adequate seizure is not triggered, the stimulus will be increased by two seconds (200 pulses) until a seizure is triggered or a maximum of 3 to 4 attempts is reached. If a seizure is not initiated in the first session, a new titration session will be scheduled. Medication will be reviewed and, if possible, the dose of benzodiazepines will be reduced depending on the opinion of the performing psychiatrist. The second titration session will repeat the same process as the first, with the parameters used in the last attempt. The maximum limit is set at 10 s of stimulation or until the coil temperature exceeds the safety limit. If no seizure is triggered in the second session, the patient will be excluded from the study. In subsequent sessions, the stimulus used will be 4 s (400 pulses) higher than the titration session, up to a maximum of 1000 pulses. If the patient has seizures of less than 20 s duration, the number of pulses will be increased by 200 pulses in the next session, until the seizures are effective or the limit of 1000 pulses is reached. These parameters were determined based on our previous experience [30].

### 2.5. Clinical and Cognitive Measures

All data will be securely stored in an electronic data capture system called Research Electronic Data Capture (REDCap) (https://redcapbrasil.com.br/).

The validated Portuguese versions of the clinical and sociodemographic assessment scales will be applied during screening, at baseline, in the active phase (after the 6th session) and during follow-up (one week, three months, and six months after the last session), as shown in Table 1. The co-primary outcome scales are the HAMD17 [17] and the Autobiographical Memory Task (AMT) [32]. Remission will be defined as a final HAMD17 score less than or equal to 7 points, and a 50% reduction in score compared to baseline assessment will be considered a response. 

Experienced neuropsychologists will perform a cognitive assessment, which will last approximately 120 min, at baseline and at follow-up (one week and six months after the last session), as shown in Table 2.

### 2.6. Safety Monitoring

Pre-anesthetic and dental evaluation will be performed before the start of the sessions. Adverse events and safety will be monitored and recorded at every study visit. To assess any adverse effects during and after the active phase of treatment, we will use the Non-Cognitive Adverse Effects Questionnaire for ECT/MST [51], which evaluates symptoms such as headaches, muscle aches, nausea, prolonged seizures, and severe events. We will also use the Young Mania Rating Scale (YMRS) [52] to assess the occurrence of (hypo)manic induction. Additionally, the Orientation Scale, a 10-item questionnaire, will be administered 30 min after each seizure treatment. Sobin et al. [53] found a positive correlation between postictal reorientation time and retrograde amnesia. If any harm occurs as a result of study participation, appropriate care will be provided to participants.

